**Flowchart 01. Recruitment and allocation scheme performed in the pilot study**

**6.4. Study design**

After randomization of the sample, the teeth (at least 20 for each group) will be allocated to one of the four assessment groups according to the scheme below:
[figure not shown]

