**Table 01: Selection criteria.**

| - INCLUSION CRITERIA | | ^x^ EXCLUSION CRITERIA |
| --- | --- | --- |
| - Presence of dentin exposure in anterior and / or posterior teeth - presence of two to four teeth with hypersensitive dentin, with a response ≥04 on the 10 cm long visual analogue scale (VAS). - Non-carious shallow lesion up to 2 mm deep, according to the Smith & Knight index (measured with a millimeter probe). (42) - Class I gingival recession according to Miller's classification. (43) | - Milk protein allergies; - Systemic diseases; - Presence of pulpitis; - Carious lesions; - Presence of parafunctional habits. - Presence of restorations in the cervical area, or defective in the tooth; - Presence of periodontal disease; - Presence of cracks or fractures in the enamel; - Patients in fixed orthodontic treatment; - Pregnant or lactating women; - Medication with analgesics; - Desensitizing treatment during the three months prior to the research recruitment date. | |

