**6.3. Sample Calculation**

To determine the sample size of the study, data from a pilot study that followed the methodology proposed in this research project was used, with four participants, three (75% of the sample) being female and one (25% of the sample) of the sample. male, with mean age of 31 years and standard deviation of ± 1.91. In the pilot study, 16 teeth were randomly assigned to one of the four groups with the Research Randomizer Calculator (www.socialpsychology.org/randomizer.htm).

The VAS was used to measure sensitivity, considering a clinically relevant difference of three units between the initial and final VAS scores, according to a previous study (20). The G Power® program (Heinrich-Heine-Universität Düsseldorf, Germany) was used for mixed ANOVA, considering a statistical power of 80%, α error of 5% and prediction of sample loss at the end of the study of 20%. The resulting sample for this study was 80 teeth, 20 teeth per group.

[figure not shown]

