**6.5. Randomization**

The participants, with at least two teeth with HD equal or superior to four in the EVA, will be allocated through a block randomization aiming to balance the sample number in the amount of existing arms. For each block a total of four participants were defined, and after the formation of the block, a numerical draw among the participants was carried out and, subsequently, each 01 volunteer was allocated to compose one of the four groups under different arrangements (A4,1 , A3.1, A2.1 and 1) (Figure 01). The total number of blocks will be ± 10.

Allocation secrecy will be maintained throughout the sampling composition process. One of the project's collaborators will be responsible for the formation of the block, numerical draw within the block and allocation in the groups. The numerical draw will be done using numbered and coded papers, of which the participants, the principal investigator, the clinical operator and the evaluator will not be aware of the group to which the participant will be allocated.

[figure not shown]

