## **6.9. Statistical analysis**

### The values ​​corresponding to the sensitivity reported by the participants were tabulated in an Excel spreadsheet (Microsoft Windows, 2010) and analyzed with the IBM SPSS Statistics for Windows 22.0 program (IBM Corp., New York, United States). Considering the parametric data of this study, if it has normal distribution of the same to the intergroup analysis will be done with mixed ANOVA, and the specific intergroup comparison will be done with the Tukey post-hoc test. If the data are abnormal distribution the intragroup comparison will be performed from the Friedman test and the intergroup by the Wilcoxon test. A significance level of 5% will be set for all analyzes to be performed.

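### Participants are randomised, but the trial is sized in teeth and analysed with no participant level; if teeth are treated as independent, the between-group test exceeds its nominal 5% error rate.

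*Protocol*

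**What the plan says.** The protocol describes the unit of allocation in two ways.

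- **Section 6.4** allocates teeth: "the teeth (at least 20 for each group) will be allocated to one of the four assessment groups".
- **Section 6.5** allocates people: "The participants, with at least two teeth with HD equal or superior to four in the EVA, will be allocated through a block randomization". It adds "For each block a total of four participants were defined", then "each 01 volunteer was allocated to compose one of the four groups", and "The total number of blocks will be ± 10".

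Sections 6.6 and 6.7.1 side with 6.5. The first speaks of the group the patient enters; the second treats the hypersensitive teeth of the subjects in a group.

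The sample is nevertheless counted in teeth. Section 6.3 says "The resulting sample for this study was 80 teeth, 20 teeth per group", with no intra-participant correlation or design effect. Table 01 requires "presence of two to four teeth with hypersensitive dentin". Section 6.2 links that limit to obtaining similar group sizes and, where a participant has more than four such teeth, keeps the most sensitive ones for the statistical analysis.

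For the analysis, section 6.9 says that if the data are normal "the intergroup analysis will be done with mixed ANOVA", followed by Tukey; otherwise Friedman within groups and Wilcoxon between groups. It mentions no participant effect, cluster adjustment or averaging per participant.

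**The concern.** Under section 6.5 treatment differs only between people. All study teeth of one participant receive the same arm, and the same person scores them on the same pain scale. Two to four scores from one mouth are therefore likely to be positively correlated, and the proper yardstick for an arm difference is the variation between participants.

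If each tooth enters as a separate replicate, the error term is too small and has too many degrees of freedom. Chance differences among about ten people per arm would then be declared treatment effects more often than the stated 5%. The sample size has the same weakness: 20 correlated teeth carry less information than 20 independent ones, so the 80% power in section 6.3 would not be delivered.

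**Working it through.** **Inputs from the protocol.** Four arms; 20 teeth per arm (6.3, 6.4); blocks of four, one participant per arm, about 10 blocks (6.5); two to four teeth per participant (Table 01); alpha 5%, power 80%, loss 20% (6.3); five assessments (6.8).

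**Assumed.** Intra-participant correlation (ICC) of 0.1, 0.3, 0.5 and 0.7. The protocol gives none.

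**1. The plan's own figure.** The loss step is consistent: 16 / 0.8 = 20 teeth per arm and 64 / 0.8 = 80 in total. The 64 evaluable teeth cannot be reproduced, because the readable text gives no SD, effect size or repeated-measures correlation. Working backwards, 16 independent teeth per arm give 80% power for a one-way effect size f of about 0.43, or for a 3-unit two-group difference with an SD of about 3.0.

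**2. Teeth per participant.** 10 blocks × 1 participant per arm = 10 participants per arm. 20 teeth / 10 participants = 2 teeth each, the Table 01 minimum. Two teeth each is therefore the case that fits the protocol's own figures.

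**3. Design effect.** DE = 1 + (m − 1) × ICC, with m teeth per participant. For ICC 0.1 / 0.3 / 0.5 / 0.7:

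- m = 2: DE 1.1 / 1.3 / 1.5 / 1.7, so 20 teeth are worth 20 / DE = 18.2 / 15.4 / 13.3 / 11.8 independent teeth.
- m = 4: DE 1.3 / 1.9 / 2.5 / 3.1, so 15.4 / 10.5 / 8.0 / 6.5.

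**4. Type I error of the between-group test.** Simulation with no treatment effect, 20,000 trials per setting, one-way four-arm F test on teeth at nominal 5%:

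| Per arm | ICC 0.1 | 0.3 | 0.5 | 0.7 |
|---|---|---|---|---|
| 10 participants × 2 teeth | 7.0% | 11.3% | 16.1% | 21.5% |
| 5 participants × 4 teeth | 11.1% | 26.7% | 39.9% | 51.6% |
| 10 participants × 4 teeth | 11.2% | 25.3% | 38.4% | 48.8% |

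Tukey family-wise rates lie within about one percentage point of these. The third row has 40 teeth per arm; it shows that the inflation depends mainly on teeth per person and that recruiting all ten blocks does not remove it. The same F test on participant means stays at about 5% in every setting.

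**5. Group-by-time test.** The mixed ANOVA over five assessments was simulated with 10 participants × 2 teeth per arm. If teeth in one mouth share only their overall level, that level cancels and the rejection rate is about 5%. If they also share their change over time (shared fraction 0.1 / 0.3 / 0.5 / 0.7), the rate is about 9 / 19 / 31 / 44%.

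**6. Power.** Take the effect size that gives 80% with 16 evaluable independent teeth per arm (f about 0.43), divide the noncentrality by DE, and use participant-level degrees of freedom. For ICC 0.3 to 0.7, power is about 64% to 52% with two teeth each and 40% to 25% with four. Scaling the 20 teeth per arm by DE gives 26 to 34 teeth (13 to 17 participants) per arm at two teeth each, against about 10 participants planned.

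**The case against.** **Section 6.9 never says that teeth are independent units.** It names mixed ANOVA without defining its error strata, and an analysis plan that is not shown could supply them. This is fair: tooth-level analysis is inferred. The inference rests on the tooth-based sample size, the selection of teeth for analysis, and the absence of a participant term from both the parametric and the non-parametric route. The contradiction between 6.4 and 6.5, and a sample size in teeth with no design effect, are in the protocol itself.

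**The larger error rates are not the planned case.** Five participants with four teeth each would need only five blocks, against about ten in 6.5. This stands: 7 to 21% is the main result, and 11 to 52% applies if participants bring four teeth. At ICC 0.1 and two teeth the excess is modest, so a reader who infers a rate far above 5% in all circumstances goes beyond what can be shown.

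**The group-by-time test may be the one that matters**, because 6.3 frames the effect as an initial-to-final difference. This stands in part: that test holds its level if teeth share only level, and the documents do not say which pattern applies.

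**The direction could reverse.** The pilot in 6.3 randomised teeth, and 6.4 repeats that wording. If teeth of one mouth were split across arms, ignoring the participant would make the between-arm tests conservative. Sections 6.5, 6.6 and 6.7.1 contradict that reading, but the protocol should settle it.

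**Confidence intervals.** A reader might conclude that the planned intervals are too narrow. The protocol plans none, so this would apply only to any that are later reported.

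**Conclusion.** The point holds, in limited form. The protocol randomises participants, sizes the trial in teeth, and fixes analyses with no participant level. Read naturally, this is a unit-of-analysis error, and for participant-level allocation with any positive ICC the between-group test is anti-conservative.

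The direction rests on two things: that section 6.5 describes the actual allocation, and that teeth enter 6.9 as separate units. The size rests on an ICC that the documents do not give. It should be reported as a range led by the two-teeth case, with the group-by-time result kept conditional on shared change over time. The quality-of-life questionnaire is completed once per participant at each of its two time points, so this point does not touch it.

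The main sensitivity comparison depends on this choice, so it should be corrected before that comparison is relied on.

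**What to change.** 1. **Sections 6.3, 6.4 and 6.5.** Reconcile them: state that participants are allocated and that all study teeth of a participant receive that participant's arm. Say that the pilot's tooth-level allocation differed.
2. **Section 6.9.** Average each participant's study teeth at each visit and run the planned analysis, including the Friedman/Wilcoxon fallback, on one value per participant. Alternatively, fit a linear mixed model with fixed arm, visit and arm-by-visit, and random participant, tooth-within-participant and participant-by-visit terms. The last term is essential. With random intercepts alone, arm-by-visit is still tested against the tooth-level residual, and the 9 to 44% inflation remains when teeth share their change over time.
3. **Section 6.3.** Restate the sample size, and the power it delivers, in participants, with an assumed ICC and design effect.

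The cost is wording and slightly more analysis in the software already named, with no new data. P-values and the stated power become less favourable. Whether to recruit more participants in response is a separate decision for the sponsor.

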**Flowchart 02. Experimental design of the study**

**Table 2.** Division of desensitizing groups and treatments.

| **GROUPS** | **DENSENSIBILIZING TREATMENT** |
| --- | --- |
| **Gplacebo** | Water-soluble placebo gel (K-Y®, Johnson & Johnson, SP, Brazil) with no active agent. |
| **GCPP-ACPF** | MI Paste Plus ™ (Recaldent ™, GC America, United States) |
| **Glaser** | Application of Laser - Photon lase III DMC |
| **GLaser +CPP-ACPF** | Application of Laser - Photon lase III DMC + MI Paste Plus ™ (Recaldent ™, GC America, United States) |

In order to standardize the initial condition, participants will be submitted to prophylaxis with rubber cup (Unid Microdont, São Paulo, SP, Brazil) and pumice stone (Maquira, Maringá, PR, Brazil). In order to mitigate possible interferences in the follow-up of the study, they received a dental hygiene kit composed of a soft bristle toothbrush (Top Plus, Condor, São Bento do Sul, SC, Brazil) and a dentifrice without desensitizing action. contains fluoride (EVEN Baby, Raimundo da Fonte Group, Paulista, PE, Brazil), with guidance on how to brush and with a frequency of at least three times a day.

**6.5. Randomization**

The participants, with at least two teeth with HD equal or superior to four in the EVA, will be allocated through a block randomization aiming to balance the sample number in the amount of existing arms. For each block a total of four participants were defined, and after the formation of the block, a numerical draw among the participants was carried out and, subsequently, each 01 volunteer was allocated to compose one of the four groups under different arrangements (A4,1 , A3.1, A2.1 and 1) (Figure 01). The total number of blocks will be ± 10.

Allocation secrecy will be maintained throughout the sampling composition process. One of the project's collaborators will be responsible for the formation of the block, numerical draw within the block and allocation in the groups. The numerical draw will be done using numbered and coded papers, of which the participants, the principal investigator, the clinical operator and the evaluator will not be aware of the group to which the participant will be allocated.

[figure not shown]

**Figure 01. Randomization scheme within a block and possible arrangements for the allocation in the arms**

**6.6. Blinding**

This study will be double-blind. The research will rely on only one operator, who has performed the experimental steps of the research. And it will involve only one evaluator to check the pain sensitivity, who will not participate in the randomization process, nor will he be aware in which group the patient will be inserted. Participants evaluated in the experiment will also not be aware of the treatment to which they will be submitted. The desensitizing gel and the placebo gel will be placed in equal containers to avoid identification by the patients of the applied product.

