**6.2. Sample selection**

Students and employees of the Federal University of Pará, Belém, Pará, Brazil, between 18 and 50 years old, of both sexes, will be evaluated and recruited at the Faculty of Dentistry of the Federal University of Pará, Belém, Pará, Brazil. The inclusion and exclusion criteria are described in Table 01.

Two calibrated dentists evaluated potential candidates. Firstly, using a tactile stimulus: by sliding an exploratory catheter 5 (Exploratory Probe, Ice, Sao Paulo, Brazil) horizontally in the mesio-distal direction and vertically in the cervico-incisal direction of the cervical third of the selected teeth, with a light force. After stimulation, patients will be asked to point the 10-cm-long analogue visual scale (VAS) at the number that describes their perception of pain (0 = absent pain and 10 = extreme pain). After five minutes, the evaluator will apply an air stimulus: throwing a 3-second air jet of a triple syringe (Triple Syringe, Dabi Atlante, São Paulo, Brazil) with ± 40psi of pressure, directed perpendicular to the surface of the lesion and 0.5 cm apart. Protecting neighboring teeth through cotton rolls or by sealing with operator's fingers. Participants will again be asked to assign the corresponding pain score on the EVA scale

He commented that the main inclusion criterion will be the presence of two to four teeth with HD, in order to obtain groups with similar sample sizes (n) and facilitate the statistical comparison. In case the patient has more than four teeth with HD, for statistical analysis will be considered those with greater sensitivity according to EVA.

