**6.7.1. CPP-ACPF and Placebo**

The subjects of G. CPP-ACPF will receive the application of the MI Paste Plus ™ gel (Recaldent ™, GC América, United States) on the vestibular surfaces of hypersensitive teeth with the aid of a Microbrush applicator (Microbrush, 3M ESPE, São Paulo, Brazil) and was maintained undisturbed for 5 min. A rubber cup mounted on a low speed handpiece will then be used to scrub the desensitizing gel for 20 seconds on each tooth as per the manufacturer's specification (http://www.mi-paste.com/apply.php) . After application of the CPP-ACPF dentifrice, the TLBP will be simulated with the positioning in two points: one in the center of the middle third and the other in the cervical third, without laser light emission, and the sound of the equipment will be mimicked with the Beep application (Foncannon Inc, Google, © 2018).

The placebo group will receive the same protocol as the CPP-ACPF group, but the gel used will be a water-soluble base with no active ingredient (K-Y®, Johnson & Johnson, SP, Brazil).

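### Equal containers do not secure participant blinding to the gel: the two products are different, no sensory match is stated, and the participants rate the outcomes themselves

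*Protocol*

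**What the plan says.** Section 6.6 of the protocol states "This study will be double-blind" and, of the participants, "Participants evaluated in the experiment will also not be aware of the treatment to which they will be submitted". For the gels it gives one specific measure: "The desensitizing gel and the placebo gel will be placed in equal containers to avoid identification by the patients of the applied product".

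Section 6.7.1 describes the active arm, whose participants "will receive the application of the MI Paste Plus ™ gel" by microbrush, with a 5-minute dwell and a 20-second rubber-cup scrub per tooth. The placebo arm follows the same steps, but "the gel used will be a water-soluble base with no active ingredient". Table 2 in section 6.4 lists that product as "Water-soluble placebo gel (K-Y®, Johnson & Johnson, SP, Brazil) with no active agent". Section 6.7 sets three sessions, 24 hours apart.

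Section 6.7.2 gives the laser arm the placebo gel before the laser, and the combined arm the CPP-ACPF product before the laser. In the two arms without active laser, section 6.7.1 provides a sham: the tip is positioned without emission and the device sound is imitated.

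Under sections 6.8 to 6.8.3 the participant gives the VAS score for the air and tactile stimuli and completes the QEHD.

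**The concern.** A container hides a label. It does nothing about what a participant sees, tastes or feels once the product is on the teeth. The measure in section 6.6 is aimed at identification by the patient, yet the operator handles the container and the patient experiences the contents. The laser sham shows that the protocol did consider masking what the participant perceives; the gel has no equivalent.

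What is at stake is expectation bias. If some participants infer whether their gel is active, their pain and quality-of-life ratings may shift. Keeping the evaluator unaware of the group does not remove a shift that arises in the participant. Nor can lost participant blinding be repaired after data collection.

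**Working it through.** The plan gives no figure to reproduce on this point. The check sets the sections side by side and counts the contrasts.

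**1. What the participant is exposed to (sections 6.7 and 6.7.1).** Dwell is 5 minutes per session over three sessions: 3 × 5 = 15 minutes, if one dwell period covers all treated teeth. The scrub is 20 seconds per tooth. With the two to four teeth of the inclusion criterion in Table 01, that is 40 to 80 seconds per session, or 120 to 240 seconds over three sessions. Contact is with the product throughout.

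**2. Whether the products are stated to match.** The active is MI Paste Plus and the placebo is K-Y, from another manufacturer, described only as a water-soluble gel or base without active agent. Sections 6.4, 6.6, 6.7.1 and 6.7.2 do not state a match in colour, taste, smell or texture, or any masking of these.

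**3. When outcomes are recorded (sections 6.8 and 6.8.3).** VAS is taken at five moments, one before treatment and four after at least one application. The QEHD is completed before treatment and at one month. Every post-baseline value therefore follows contact with the gel.

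**4. Which contrasts are exposed.** Four arms give 4 × 3 / 2 = 6 pairs. Two arms receive the placebo gel (placebo, laser) and two receive CPP-ACPF (CPP-ACPF, laser + CPP-ACPF), so 2 × 2 = 4 pairs differ in gel and 2 share it:

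| Contrast | Gel differs? |
| --- | --- |
| CPP-ACPF v placebo | Yes |
| Laser + CPP-ACPF v laser | Yes |
| Laser + CPP-ACPF v placebo | Yes |
| CPP-ACPF v laser | Yes |
| Laser v placebo | No |
| Laser + CPP-ACPF v CPP-ACPF | No |

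The exposed set includes the combination against placebo, which is central to the aim in section 5. The post-hoc comparisons between groups in section 6.9 would draw on these pairs.

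**5. Whether one person can compare the gels.** Section 6.5 allocates each volunteer to one group, so each person meets one gel. Section 6.4 speaks of allocating teeth, as was done in the pilot described in section 6.3. Read that way, both gels could be used in one mouth and the risk would be greater. The conclusion below takes the participant-level reading, which is the more favourable one.

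**The case against.** The strongest reply is that the masking is better than the container alone suggests. Application method, dwell and scrub are common to all arms, and everyone receives a gel and a real or apparent laser. Allocation is concealed by coded papers. Under section 6.5 a participant meets one gel and has no comparator. Noticing a texture is also not the same as unblinding, because the participant must still infer that the gel is active or inactive. All of this stands and lessens the risk. It does not make the container an effective mask, since a single product may still be judged to be, or not to be, a dental paste.

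Some stronger readings are tempting, but the documents do not support them:

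- **That participants will identify the gel.** The protocol describes the sensory properties of neither product. Section 6.7.1 does write "After application of the CPP-ACPF dentifrice", but it also calls the same product a gel, and participants do not read this text.
- **That recruits know the products.** Section 6.2 says students and employees of the university "will be evaluated and recruited at the Faculty of Dentistry of the Federal University of Pará". That fixes the place of recruitment; it does not make them dental students or dental staff.
- **That the bias can be sized.** Multiplying a share who recognise the gel by an expectation gap would need two inputs that the protocol does not give. The three VAS units in section 6.3 are no yardstick either, because they describe a change from initial to final score, whereas this bias would be a difference between arms.
- **That only the two contrasts differing in gel alone are affected.** The table above shows four.

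**Conclusion.** The point holds as a defect in the stated masking measure. Equal containers cannot do what section 6.6 says they do. With different products, no stated sensory match and self-rated outcomes, participant blinding is not secured for four of the six pairwise contrasts. Laser v placebo, and the combination v CPP-ACPF, are not affected by this point.

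This rests on the text of the protocol and on participant-level allocation. It does not establish that unblinding will occur, and no magnitude can be derived from the documents. It goes beyond missing detail, because the protocol names a measure and a purpose and the one does not serve the other. The change is worth making before enrolment.

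**What to change.** In section 6.6, replace reliance on the container with three provisions:

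1. Match the inactive gel to the active product in colour, flavour and consistency, or state how these are masked, in both the placebo arm and the laser arm.
2. Ask each participant which gel they think they received, directly after the first application and before the first post-treatment VAS. Report the answers by arm, descriptively. Do not stratify the treatment contrasts by the answer: it arises after randomisation and treatment may influence it. Asking after the third session would be worse, since by then the guess may reflect relief already felt.
3. If no match is made, do not describe the four contrasts that differ in gel as participant-blind, and qualify the double-blind statement to that extent.

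The cost is some gel preparation, with confirmation that the prepared gel remains inactive, and one extra question at a visit already planned. The blinding claim may also become less favourable.
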